### Sample size and data analyses

The study outcomes will be analysed according to ‘Intention-to-treat’ (ITT) principles. Specifically, the sample to be analysed is defined as all users who have provided a usual consumption unit within 4 weeks after completing the baseline questionnaire. Over-recruitment will compensate for participants failing to provide a consumption unit within this period. According to ITT principles, only those participants who provided their baseline data, including their usual consumption unit, will be included in the analyses.

To examine between-group differences with a t-test, the required sample size of this study was calculated assuming a power of 80%, a 5% alpha error, and a THC standard deviation equal to one-third of its mean (approximated using Canadian data,
^43^; adding 25% to account for uncertainty). The required sample size was estimated to sum up to n=698 participants (control: n=349; intervention: n=349) for detecting group differences in THC exposure.

Not relevant for sample size considerations, we expect that 20% (control: 30%; intervention: 10%) of all participants of the ITT sample will be lost to T12 follow-up. Subjects dropping out of the study will not be replaced and missing values will be imputed using the ‘Last Observation Carried Forward‘ (LOCF) technique. The critique regarding LOCF imputation methods
^44^ does not apply to our study, as this method will bias the data towards the null hypothesis (assuming no change over time) and therefore representing a conservative imputation approach. The assumptions of LOCF will be examined in sensitivity analyses using advanced multiple imputation techniques.

To evaluate both aspects of the primary outcome, two analyses need to be conducted. First, the THC exposure levels in the past 30 days ascribed to illegal cannabis acquisition within the intervention group needs to be compared between baseline and intervention, with a 50% reduction denoting the minimum threshold for a positive evaluation. Second, a between-group comparison of THC exposure in the past 30 days at T12 adjusting for baseline data will be conducted using a t-test. The dependent variable will be calculated as follows:

$$THC_{T12–adjusted}=\frac{THC_{T12}*100}{THC_{T0}}$$

The actual between-group comparison will be evaluated against the following condition:

$$THC_{T12–adjusted–interventiongroup}<=0.9*THC_{T12–adjusted–control\;group}$$

Multilevel regression analyses will be performed additionally for evaluating the primary outcome, which serve to rule out the impact of possibly confounding variables. For evaluating the secondary outcomes, the proposed analyses (correction for baseline values, comparison via t-test, confirmation via multilevel regression analyses) will be performed analogously.

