**Figure 1. f1:**
[figure not shown]
Study flow chart.

Prior to any data collection, study team members will take consent of each participant. A model consent form is available as
*Extended data*
^31^. In both study groups, participants will be asked to complete a questionnaire and provide their usual consumption unit (e.g., joints, mix of tobacco and cannabis to smoke in water pipe, etc.) at both baseline and again after one year (T12). In predetermined intervals, additional questionnaires will be completed by all participants. Further, individual sales data will be collected for intervention group participants, which will be part of the primary outcome analyses.

All participants will be recruited via posters, or through consumer groups and local stakeholders in each city. To incentivize study participation and minimize loss to follow-up, participants will be reimbursed with 25€ upon completion of the questionnaires at each wave. Further, providing details regarding their usual consumption unit will be reimbursed with 15€ (at baseline and at one-year follow-up).

Every resident in the respective control or intervention municipality aged 18 years or above reporting to have used cannabis at least monthly in the past 6 months may participate in the study. Following international recommendations to minimize cannabis use risks
^32^, persons with a familial predisposition to psychotic or substance use disorders, pregnant women, persons in current psychiatric treatment or with a preceding psychotic disorder will be excluded from this study. Further, persons with a prescription to use cannabis for medical purposes will not be eligible to participate as the study focuses on recreational use only.

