### Primary outcome

Two important aspects will determine the study’s success and will be combined in the primary outcome, measured at baseline and at 12-month follow-up: 1) dominance of legal over illegal consumption, and 2) reduction of THC exposure. The hypothesis for the primary outcome is:

“As compared to baseline, intervention group participants will reduce their use of illegally acquired THC within the past 30 days by at least 50% at 12-month follow-up. Taking into account baseline exposure levels, the total amount of THC consumed among
*intervention* group participants within the past 30 days will fall below the total amount of THC consumed among
*control* group participants within the past 30 days by at least 10% at 12-month follow-up.”

As first aspect, we expect that illicit cannabis use will be largely replaced by consumption of legally acquired products. A shift from an illegal to a legal consumption environment implies that exposure to contaminants and pollutants but also legal consequences (revocation of driver’s licence, imprisonment) will be largely diminished or even completely prevented. As an evaluation of changes in these specific outcomes would require very large sample sizes, and go beyond the scope of this study, we will restrict the first part of the primary outcome to a proxy, i.e., to the percentage of legal cannabis consumption. This will be operationalized as the percentage of an individual’s THC exposure within the past 30 days acquired through purchases in pharmacies.

For the second aspect, we expect to halt the increasing THC exposure among intervention group users. While THC levels in seized and legally available cannabis products are increasing, intervention group participants are expected to reduce their overall THC consumption as compared to control group participants. While THC exposure is the core determinant for cannabis-attributable harm, specific effects on adverse consequences (e.g. on incidence of psychotic disorders) require larger sample sizes which, again, are beyond the scope of this study.

While the first aspect will only be evaluated within the intervention group, the second aspect will require between-group comparisons across a 12-month period. Only if both aspects can be positively evaluated, can an overall success of the study be inferred.

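### The sample size of 698 at 80% power cannot be derived from the printed inputs, and the stated SD is for THC, not for the T12/T0 ratio that is tested

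*Protocol article*

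**What the plan says.** All sample size statements are in the protocol article, section Sample size and data analyses.

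- Test and power: "To examine between-group differences with a t-test, the required sample size of this study was calculated assuming a power of 80" per cent.
- Type I error: "a 5% alpha error". Sidedness is not stated.
- Variability: "a THC standard deviation equal to one-third of its mean", approximated from Canadian data, with the remark "adding 25% to account for uncertainty".
- Result: "The required sample size was estimated to sum up to n=698 participants (control: n=349; intervention: n=349) for detecting group differences in THC exposure".
- Expected loss to T12 (20% overall; 30% control, 10% intervention) is introduced with "Not relevant for sample size considerations".

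The sample size sentence names no effect. The only between-group effect in the article is in Primary outcome, where intervention exposure is to fall below control exposure "by at least 10% at 12-month follow-up". It reappears as the factor 0.9 in the decision condition.

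The variable tested is each participant's T12 exposure times 100 divided by that participant's T0 exposure. Under Assessment details, exposure is THC per usual consumption unit times the number of use occasions in 30 days. Under Study design, sample and recruitment, any adult resident "reporting to have used cannabis at least monthly in the past 6 months may participate in the study", subject to the exclusions, so use frequency may vary widely.

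**The concern.** The article prints both inputs and result, and they do not agree. This is therefore not detail left to a fuller document: a reader who puts the printed inputs into the standard formula gets a different number.

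There is a second, separate gap. The SD is described as that of THC, but the test is on a within-person ratio. The SD of a ratio depends on the exposure CV and on how strongly T12 tracks T0, and the article gives no figure for either on the scale that is tested.

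Overall success requires both aspects of the primary outcome, and this comparison is the second. If its power is not known, a non-significant result cannot be read as evidence of no reduction, and the main justification for the size of the trial cannot be checked.

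**Working it through.** **Inputs.** From the sample size paragraph: power 80%, alpha 5%, SD/mean (CV) = 1/3, a 25% allowance, equal arms of 349. From Primary outcome and the 0.9 condition: difference 10% of the mean (inferred). Two-sided testing is assumed; one-sided is also shown.

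**Step 1: try to reproduce 349 per arm.** Normal approximation: n per arm = 2 × (1.960 + 0.8416)² × (CV/0.10)² = 2 × 7.849 × (CV/0.10)². The exact t-test adds about one per arm.

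| Reading | CV | Normal n per arm | Exact t, per arm | Total |
|---|---|---|---|---|
| 25% already inside the one-third | 0.333 | 174.4 | 176 | 352 |
| 25% added to the SD | 0.417 | 272.5 | 274 | 548 |
| 25% added to n (176 × 1.25) | 0.333 | – | 220 | 440 |
| One-sided | 0.333 | – | 139 | 278 |
| One-sided, 25% on the SD | 0.417 | – | 216 | 432 |

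None gives 698. Exact two-sided power at 349 per arm is 97.7% for CV 0.333 and 88.6% for CV 0.417.

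**Step 2: what would give 349.** Solving for 80% power at 349 per arm gives a standardised difference of 0.2124. At a 10% difference that is CV = 0.10/0.2124 = 0.471. Alternatively, the effect would be 0.2124 × 0.333 = 7.1% at CV 0.333, or 0.2124 × 0.417 = 8.8% at CV 0.417. Possible routes to 698 or near it:

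- CV = √2/3 = 0.471 gives 2 × 7.849 × 0.2222/0.01 = 348.8, so 349 per arm. This is the approximate SD of a T12/T0 ratio, or of a change, when the correlation is zero.
- 2 × 174.4 = 348.8 is also the two-arm total for CV 1/3, so a total used as a per-arm number would give the same figure.
- CV 0.417 with dropout: 274/0.8 gives 343 per arm (686), or 274/0.7 + 274/0.9 gives 392 + 305 = 697. The text says dropout was not considered and states equal arms.
- The 25% used twice: 274 × 1.25 gives 343 per arm (686).

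None of these is stated in the article.

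**Step 3: power for the variable tested.** If T0 and T12 have the same CV and correlation rho, the delta method gives CV of the ratio ≈ CV × √(2(1 − rho)). The table uses the exact two-sided t-test with a common SD, 349 per arm and a 10% difference.

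| Exposure CV | rho 0 | rho 0.5 | rho 0.8 | rho 0.9 |
|---|---|---|---|---|
| 0.333 (stated) | 80% | 97.7% | >99% | >99% |
| 0.417 (stated, plus 25%) | 61% | 89% | >99% | >99% |
| 0.68 (assumed) | 28% | 49% | 87% | 99% |
| 1.07 (assumed) | 14% | 23% | 50% | 79% |

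The two larger CVs are illustrations, not document figures. Use days spread evenly over 1 to 30 have CV 0.56. Combined with an independent CV of 1/3 for THC per unit, √[(1 + 0.56²)(1 + 0.333²) − 1] = 0.68. An equal mix of 1, 4, 12 and 30 occasions has CV 0.96, and the same formula gives 1.07. Reading the one-third as THC per unit is itself an assumption. The delta method is rough at large CVs; for CV 0.417 and rho 0, a lognormal calculation gives about 58% instead of 61%.

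**The case against.** The strongest reply is that the printed inputs are incomplete. The 10% effect and the two-sided test are inferred, and the article says that a full-length proposal exists, where the formula and correlation may be given. An effect of 7.1% or 8.8% would also make 349 correct. This stands as a limit on wording: the point is that 698 cannot be derived from what is printed, not that 698 is wrong. It does not remove the point, because the article states no other between-group effect and a one-sided test moves further from 698.

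A second reply is that 349 matches an SD of √2/3 exactly, so the planners may already have converted to the ratio scale with zero correlation. That cannot be excluded. A reader might instead infer that a two-arm total was entered as a per-arm number. The documents do not support that choice, because both routes give 348.8. On the conversion route the 25% must already be inside the one-third; if it comes on top, zero correlation needs 1,092 in total.

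A reader might also infer that the trial is underpowered because users range from monthly upwards. The documents do not support that either. Dividing by a person's own baseline removes stable differences between people, and the result turns on a correlation that is not given. At the assumed CV of 0.68, power runs from 28% to 99%. The opposite inference, that 698 is larger than needed, holds only if the stated SD applies to the tested ratio, which is not shown.

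**Conclusion.** The point holds in two parts. First, given a 10% difference and two-sided 5% alpha, the printed inputs lead to 352 or 548 participants, not 698, and to 97.7% or 88.6% power at 349 per arm, not 80%. The missing element is an SD of 0.471 of the mean or something equivalent. The text does not say what it was, and it rules out dropout.

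Second, the 80% is unsupported for the T12/T0 ratio. Over the CVs and correlations shown, power at 349 per arm runs from 14% to above 99%. With the article's own inflated CV of 0.417 it is 61% at zero correlation and 89% at 0.5. The direction of the error is therefore open, and neither underpowering nor oversizing is established.

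**What to change.** Keep N=698. Recompute and rewrite the sample size paragraph so that it states:

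- the between-group effect and whether the test is one- or two-sided;
- whether the 25% is already inside the one-third, is added to the SD or is added to n;
- the SD of the quantity actually analysed (the T12/T0 ratio), with the assumed T0–T12 correlation;
- the step that leads from these inputs to 349 per arm, so that a reader can repeat it.

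Then replace the single 80% by the power that 698 participants give over a stated range of SD and correlation.

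The cost is a recalculation and a reworded paragraph, with no extra participants. The stated power may turn out less favourable. The article describes version 1, with the federal authority's decision pending and ethics review still to come, so the correction can be made before the study starts.

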### Secondary outcomes

For secondary outcomes, we will adhere to the criteria proposed to evaluate the legalization of cannabis in Canada
^41^, encompassing all cannabis use behaviours linked to adverse consequences, for which substantial evidence exists
^32^. As intervention group participants will receive information on risky cannabis use
^32^ and enclosed within each cannabis package sold by the pharmacies, we hypothesize that risky cannabis use practices will not increase among these users – despite the presumably increased availability of cannabis products. Specifically, we hypothesize that intervention group participants will: A) not increase their use frequency, B) not increase frequency of THC-impaired driving, and C) will not smoke cannabis products more frequently (for operationalization, see
Table 1). The secondary outcomes will be evaluated at one-year follow-up, which involves testing for differences between control and intervention group while taking baseline values into account.

**Table 1. T1:** Operationalization of secondary outcomes.

Indicator	Operationalization
A) Frequency of use	Number of use days in the past 30 days
B) THC-impaired driving	Number of occasions on which a vehicle was driven within six hours after using cannabis in the past 30 days
C) Mode of administration	Percentage of all use units using combustible methods, such as smoking joints, blunts, (water) pipes

As further secondary outcomes, we will examine acceptance and satisfaction of the dispensary model among intervention group participants, which may be important for explaining a possible dominance of illegal over legal consumption (see first aspect of primary outcome).

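### LOCF is not conservative for the between-group THC comparison: with 30% control and 10% intervention dropout, the direction of bias depends on the trend common to both cities

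*Protocol article*

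**What the plan says.** Under Sample size and data analyses, the protocol article imputes missing values by LOCF. It holds that published criticism of LOCF has no bearing on this study, because "this method will bias the data towards the null hypothesis (assuming no change over time) and therefore representing a conservative imputation approach". Multiple imputation is planned only as a sensitivity analysis, and the article does not say what follows if it disagrees.

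The same paragraph expects that "20% (control: 30%; intervention: 10%) of all participants of the ITT sample will be lost to T12 follow-up", and introduces this with "Not relevant for sample size considerations".

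The primary outcome has two aspects, and both must succeed:
- Aspect 1 is a fall of at least 50% in illegally acquired THC within the intervention group.
- Aspect 2 requires total THC in the intervention group to lie below that of the control "group participants within the past 30 days by at least 10% at 12-month follow-up". It is tested by a between-group t-test on 100 × T12/T0 and judged against intervention ≤ 0.9 × control.

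Under Assessment details, consumption units are analysed at baseline and T12 only. Questionnaires are given at T0, T3, T6 and T12.

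For the secondary outcomes, "we hypothesize that risky cannabis use practices will not increase among these users". These are analysed in the same way as the primary outcome.

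**The concern.** The justification uses one null hypothesis for two different questions. Carrying baseline forward pulls each group towards no change. Where the question is whether the intervention group changed (aspect 1), that pull works against success. Where the question is whether two groups changed differently (aspect 2), the pull cancels only if both groups are affected equally. Here three times as many controls as intervention participants are expected to be held at T12/T0 = 100, so any trend shared by both cities appears as a difference between them.

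If use falls in both cities, the controls' fall is masked more and the intervention looks better than it is. If use rises in both, the controls' rise is masked more and a real benefit is hidden. Since LOCF governs the primary decision, the study could report a relative reduction that reflects dropout, or miss one that is real.

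For the secondary outcomes the hoped-for finding is no increase, so a pull towards no change is not automatically the cautious direction.

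**Working it through.** **Inputs from the protocol.** 349 per group; dropout 30% control and 10% intervention; outcome T12/T0; threshold 0.9; "assuming a power of 80%, a 5% alpha error"; "a THC standard deviation equal to one-third of its mean", with "adding 25% to account for uncertainty".

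**Assumptions.** Dropouts take their baseline value (ratio 1.00), as the protocol's no-change reasoning implies. Dropout is unrelated to outcome. The documents give no figure for the common change m, so a range is shown.

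**The plan's own sample size.** n per group = 2(1.960+0.842)² SD²/0.10². SD = 1/3 gives 175, SD = 1.25/3 = 0.417 gives 273, and SD = √2/3 = 0.471 gives 349. The stated 349 is matched only by the last, which the text does not describe. All three SDs are therefore carried below.

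**Expected ratio with no true effect.** The intervention mean is 0.9m+0.1 and the control mean 0.7m+0.3. Their ratio equals 1 only when m = 1.

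| Common change | Ratio under LOCF |
|---|---|
| −10% | 0.91/0.93 = 0.978 |
| −20% | 0.82/0.86 = 0.953 |
| −30% | 0.73/0.79 = 0.924 |
| −37% | 0.667/0.741 = 0.900 |
| +10% | 1.09/1.07 = 1.019 |
| +20% | 1.18/1.14 = 1.035 |

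The threshold is reached where 0.9m+0.1 = 0.9(0.7m+0.3), so m = 0.17/0.27 = 0.63.

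**Simulated rates with no true effect.** SD 1/3 to 0.471; normal or lognormal ratios; SD constant or proportional to the mean.

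| Common fall | t-test significant for intervention (nominal 2.5%) | ≤ 0.9 condition met |
|---|---|---|
| 10% | about 9–16% | 0–1% |
| 20% | about 22–57% | 0.3–7% |
| 30% | 44–70% (constant SD) | 20–28% (constant SD) |
| 37% | not tabulated | about 50% |

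**Rising trend with a real effect.** Let control rise 11% (m = 1.111) and intervention stay flat, a true ratio of 0.90. Under LOCF, control is 0.7 × 1.111 + 0.3 = 1.078 and the ratio is 1/1.078 = 0.928. In simulation the ≤ 0.9 condition is met in about 9–16% of trials.

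A normal approximation agrees. The quantity intervention − 0.9 × control has mean 1 − 0.9 × 1.078 = 0.030. Its variance is [0.9 SD² + 0.81(0.7 SD² + 0.21 × 0.111²)]/349. This gives 8%, 13% and 16% for the three SDs. Without dropout the figure is about 50%, because the true ratio lies exactly on the threshold.

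**Secondary outcomes, baseline carried forward.**
- Intervention 1.0, control 0.9: control becomes 0.93, so +10 points shrinks to +7. Power to detect the harm falls from 80% to 60% (SD 0.471).
- Intervention 1.1, control 1.0: intervention becomes 1.09, so +10 becomes +9. Power is essentially unchanged at 79%.
- Both 1.1: 1.09 against 1.07, a spurious +2 points against the intervention.

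**Aspect 1.** With 10% held at baseline, completers must fall by 50/0.9 = 55.6% for the group to show 50%. Here LOCF is conservative.

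**The case against.** The strongest defence is that the protocol expects exposure to rise, and under a rising trend LOCF works against the intervention on aspect 2, as it does on aspect 1. Eligibility requires only monthly use, which is weak selection for regression to the mean. The individual-ratio outcome also pushes the other way: with no change, a coefficient of variation of 1/3 and a T0–T12 correlation of 0.7 down to 0, completers' mean ratio is 1.03–1.11 while dropouts sit at 1.00. Multiple imputation and multilevel regression are already planned.

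Much of this stands. It shows that LOCF is cautious in one scenario, not that it is cautious whatever the trend. In that same scenario it can also defeat a trial that reaches its target. A sensitivity analysis with no stated consequence does not change the primary decision.

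Three stronger readings are tempting but unsupported:
- A reader might infer that LOCF creates a fall within the intervention group. It cannot; any false benefit is relative to control.
- A reader might take the t-test error rates as the chance of falsely declaring success. They are not. The plan also requires the ≤ 0.9 condition and aspect 1, and dropout alone rarely meets the 0.9 condition below a common fall of about 30%.
- A reader might infer that LOCF always favours the no-increase hypotheses. The effect is small if only the intervention group rises and reverses if both rise equally. T3 and T6 questionnaires may also supply post-baseline values to carry forward.

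**Conclusion.** The unconditional claim that LOCF is conservative is wrong for aspect 2. It holds for aspect 1 if baseline is carried forward, and for aspect 2 in direction only if exposure rises in both cities. With the protocol's own dropout rates, the null ratio is 0.978 at a common 10% fall and 0.953 at 20%, and t-test error in the intervention's favour is well above nominal. The 0.9 condition is at material risk only from a common fall of about 30%. Under the expected rise, a true 0.90 is diluted to 0.928. The statement that attrition does not matter for the sample size therefore fails too: N stays at 698, but the effect it was sized to detect shrinks. For the secondary outcomes the concern holds in some scenarios only.

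These sizes rest on baseline being carried forward, dropout unrelated to outcome, an SD of 1/3 to 0.471, and an assumed common trend that the documents do not quantify.

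**What to change.** Make the already planned multiple imputation the primary analysis. Impute by group, using the T0, T3 and T6 questionnaires, the baseline consumption unit and, for the intervention group, the sales data. Add delta-adjusted sensitivity analyses with separate shifts for each group, so that departures from missing at random can differ between cities. Keep LOCF as a sensitivity analysis only.

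Delete the sentence that calls LOCF conservative and dismisses its critique, and delete the phrase stating that attrition has no bearing on the sample size.

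The cost is protocol and analysis-plan wording plus modest analysis work; no new data are needed. The downside is wider standard errors, which reflect the information actually lost.

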## Abstract

**Background: **New approaches are required to slow down or reverse increasing trends of levels of delta-9-tetrahydrocannabinol (THC) and cannabis-attributable hospitalizations in Germany. Legal access to cannabis may constitute one viable effective policy response; however, available evidence does not suffice to inform a regulation model for Germany. The proposed study aims to reduce harm for cannabis users through legal access to herbal cannabis through pharmacies.

**Protocol:** A quasi-experimental study comparing cannabis users with legal access to herbal cannabis (Berlin, intervention group) to those without legal access (Hamburg, control group) (total N=698). As the primary outcome, we hypothesize that: 1) illegal THC consumption will reduce by at least 50% in the intervention group and 2) total THC exposure in the intervention group will be reduced by at least 10% lower than that of the control group, taking into account baseline values. Secondary outcomes comprise measures of frequency of use, THC-impaired driving, and mode of administration. Paired t-tests and multilevel regression models will be performed for statistical analyses.

**Discussion: **This study proposal is currently being reviewed by the ‘Federal Institute for Drugs and Medical Devices’ – the body responsible for approving research studies on classified substances, including cannabis. Upon approval and prior to the start of the study, a full ethical review will be undertaken. Results may inform a regulation model for Germany and other jurisdictions and are expected to deepen the understanding of the effects of legal access to cannabis.

**Pre-registration: **German Clinical Trials Register (DRKS), DRKS00020829

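### The stated 80% power is for detecting a group difference in THC exposure, not for the 0.9 × control condition that decides aspect 2 of the primary outcome

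*Protocol article*

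**What the plan says.** Two parts of the Protocol article bear on this.

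- **Sample size and data analyses, planning.** For a between-group t-test, "the required sample size of this study was calculated assuming a power of 80%, a 5% alpha error" and a THC standard deviation of one-third of the mean, with 25% added for uncertainty. The result is 349 per group (698 in total), described as the number "for detecting group differences in THC exposure". The size of the difference is not given, nor whether the test is one- or two-sided.
- **Sample size and data analyses, decision.** Each person's T12 exposure is expressed as a percentage of their T0 exposure and compared between groups by t-test. Then: "The actual between-group comparison will be evaluated against the following condition", with the intervention value required to be no more than 0.9 times the control value. The text does not say whether this applies to the observed means or to a confidence limit.
- **Primary outcome.** The hypothesis is that intervention exposure will fall below control exposure "within the past 30 days by at least 10% at 12-month follow-up". Overall success needs both this aspect and the one on illegal THC, so failing the 0.9 condition is enough to fail the study.

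**The concern.** A t-test for a group difference has no difference as its null value. The success condition has 0.9 as its boundary. These are different criteria, and a power figure calculated for the first says nothing about the second.

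The gap matters because 10% appears in the document both as the hypothesised effect and as the hurdle. An estimate centred on a hurdle falls on the wrong side of it about half the time, and a larger sample does not help. A reader who takes the 80% at face value would think that a dispensary model delivering a 10% reduction has four chances in five of being judged successful on this aspect. It has at most about one in two. How the inequality is applied is also open, and at a true 10% that choice moves the chance of success from about 50% to 5% or less. It should not be made after the data are known.

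**Working it through.** **Inputs.** From Sample size and data analyses: 349 per group, power 80%, alpha 5%, SD one-third of the mean. From Primary outcome: a reduction of at least 10%. Assumptions: control mean scaled to 1; SD s equal in both groups; sample means approximately normal. The 25% can be read in more than one way, so three SDs are used: 1/3 as printed; 1/3 × 1.25 = 0.417; and √2/3 = 0.471, which the text does not state but which reproduces the sample size (step 1).

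**Step 1. The plan's own figure.** For a 10% difference from zero, two-sided 5%, 80% power:

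n per group = 2 × (1.960 + 0.842)² × s² / 0.10²

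| s | n per group for 80% power | power with 349 per group |
|---|---|---|
| 1/3 | 175 | 97.7% |
| 0.417 | 273 | 88.7% |
| 0.471 | 349 | 80.0% |

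The printed SD does not lead to 349 per group for a 10% difference, and neither does that SD raised by 25%. Only the unstated 0.471 does so exactly. The planning effect therefore cannot be recovered from the text.

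**Step 2. The decision rule.** Let D = (intervention mean) − 0.9 × (control mean). The condition is D ≤ 0. Its standard error is

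SE(D) = s × √((1 + 0.81)/349) = 0.0720 × s

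This is 0.0240, 0.0300 and 0.0339 for the three SDs.

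**Step 3. Chance of success at a true ratio of 0.90.** The expected value of D is 0.

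- Point-estimate rule: P(D ≤ 0) = Φ(0) = 50%, for every s and every n. Simulation with 20,000 trials per SD gave 49.8% to 50.2%.
- Point-estimate rule plus a significant t-test against zero: still 50%. The smallest significant difference is 0.049 to 0.070, so any result that meets the 0.9 condition near these means is already significant.
- 0.9 as the tested bound: 2.5% at two-sided 5%, or 5% at one-sided 5%, because the truth lies on the null boundary.

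**Step 4. True ratio needed for 80% success with 349 per group.**

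- Point-estimate rule: 0.9 − 0.842 × SE(D)
- 0.9 excluded at two-sided 5%: 0.9 − (1.960 + 0.842) × SE(D)

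| s | point estimate ≤ 0.9 | 0.9 excluded, two-sided 5% |
|---|---|---|
| 1/3 | 0.880 (12.0% reduction) | 0.833 (16.7%) |
| 0.417 | 0.875 (12.5%) | 0.816 (18.4%) |
| 0.471 | 0.871 (12.9%) | 0.805 (19.5%) |

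If the SD scales with the group mean, the first entry of the last column becomes about 0.839 (16.1%). Hence the rounded ranges of 12–13% and 16–20%.

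The printed SD describes THC exposure, whereas the analysed variable is the individual ratio T12/T0, whose SD the article does not give. The figures in step 4 depend on that SD. The 50%, 2.5% and 5% do not.

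**The case against.** The strongest reply is that the hypothesis says at least 10%. On that reading 10% is the minimum worth calling a success, not the effect the sponsor expects, and any threshold rule fails about half the time when the truth sits exactly on the threshold. With a true reduction of 15%, the point-estimate rule would be met 93–98% of the time over the three SDs. This is correct, and it is why the 50% must be stated as conditional on a true reduction of exactly 10%. It does not rescue the 80%: the document names no larger expected effect, and it attaches the power to detecting a difference rather than to the 0.9 condition. If 0.9 were the tested bound, even a true 15% would succeed only 31–55% of the time (two-sided 5%, equal SDs).

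It can also be said that the article condenses a longer proposal which may hold the missing inputs. That excuses brevity. It does not excuse a test, a power, a sample size and a success inequality that are all printed here and do not fit together.

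Four stronger readings are tempting, and the document does not support them.

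- *That the 80% was calculated for 10% against zero.* No effect size is printed, and at the printed SD the power for 10% would be about 98%.
- *That the illegal-THC aspect has the same flaw.* The abstract lists paired t-tests without tying them to a null of zero change. The analysis section gives a 50% threshold but no planning effect or power for it. A paired test against a 50% reduction is not excluded.
- *That a significant reduction of, say, 6% would have no verdict.* It would fail the 0.9 condition, and so would not count as success.
- *That joint power for the two aspects is wrongly missing.* An article may leave that to the full proposal or the analysis plan.

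**Conclusion.** The point holds in conditional form, and the text is wrong as written: the stated power does not belong to the criterion that decides aspect 2. If the true reduction equals the hypothesised minimum of 10%, the chance of meeting the criterion is about 50% on the point estimate, and 2.5% or 5% if 0.9 is tested, against a stated 80%. These values need only approximately normal sample means. The true reductions that would give 80% success with 349 per group, about 12–13% or 16–20% depending on the rule, rest on assumed SDs of 1/3 to 0.47 of the mean and should be recalculated once the SD of the T12/T0 ratio is stated.

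**What to change.** In Sample size and data analyses, state the true between-group effect, the SD of the analysed variable and the sidedness assumed for the sample size. Then adopt one of two rules before data are seen.

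- **(a) Keep 0.9 as the hurdle.** Test H0: intervention mean ≥ 0.9 × control mean, with success if the upper confidence limit of the ratio is at or below 0.9. Replace the 80% claim with the true reduction for which this rule has 80% power at 349 per group.
- **(b) Treat 10% as the planning effect only.** Define success as the confidence interval for the group comparison excluding no difference, drop the 0.9 condition, and restate the power from the stated inputs. The hypothesis in Primary outcome and in the Abstract then needs matching wording, because success would no longer show a reduction of at least 10%.

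The cost is wording, plus a less favourable stated power under (a) or a weaker claim under (b). No extra participants are needed. By its own account the study still awaits regulatory approval and ethical review, so the change can be made before it starts.
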